### Strategies for study retention

All participants will receive a text message informing them of the date, time, and place for the next outpatient clinic until the end of the study period. In case of no-shows, personal calls to the participant will be made to encourage attendance.

### Data analysis

All statistical analyses will be performed using Statistical Package for the Social Sciences version 25.0 for Windows (IBM, Armonk, NY). The participants’ demographic characteristics will be analyzed using descriptive statistics. After verifying the normality, the Student t-test or Mann–Whitney *U* test will be used to analyze the numerical data. For categorical data, we will use the chi-squared test or Fisher’s exact test. All results with a p-value of less than 0.05 will be considered as significant.

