**Discussion:**

This trial may not only provide evidence on the efficacy of a 5% lidocaine patch for acute postoperative pain management after unilateral inguinal hernia repair, but also demonstrate the efficacy and safety of the patch for post-discharge pain management.

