### Outcomes

The primary outcome is pain intensity measured using the VAS at the time of discharge from the day surgery unit, which is approximately 2 or 3 h after the surgery. We will evaluate each patient’s VAS scores in three situations: at rest, when coughing, and when moving. The secondary outcomes are pain intensity at 24 h and 1 week after surgery. We will evaluate each patient’s VAS score when they visit the clinic for wound dressing on the first postoperative day when the pain-relieving effect of the patch has been worn off. At the follow-up visit 1 week after surgery, we will assess the VAS score, the rates of postoperative complications (such as nausea, vomiting, and desaturation), and the total amount of oral combination analgesics used after discharge. To understand the correlation with general anesthesia and lidocaine patch, we will additionally analyze the amount of intraoperative opioid use, time to recovery, and pain intensity at 30 min after surgery as a part of the secondary outcomes. The participants’ demographic characteristics, such as age, sex, body weight, and height, will also be recorded.

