Through these studies, which included randomized clinical trials and meta-analyses, the safety and efficacy of using a 5% lidocaine patch for acute postoperative pain management has been established. However, most of these studies were on patients who received hospital care and patient-controlled analgesia following surgery, in which the patients’ acute pain was rapidly treated by medical staff. However, the lidocaine patch has advantages comparing with other operative pain managements, such as abdominal muscle fascia and peritoneal nerve block and patient-controlled analgesia. It is non-invasive and simple to apply since the lidocaine patch may produce an analgesic effect without a complete sensory blockage by penetrating skin depth of only 8 to 10 mm [15]. The lidocaine patch may also have a great safety profile for application in an outpatient clinical setting for acute postoperative pain.

We have designed this clinical trial to investigate the efficacy of a 5% lidocaine patch for postoperative pain management without additional medical attention. Therefore, we will enroll patients undergoing open unilateral inguinal hernia repair at a day surgery unit. We believe that in addition to demonstrating the efficacy of a 5% lidocaine patch on acute postoperative pain after unilateral inguinal hernia repair, we will be able to provide evidence on its efficacy and safety for post-discharge pain management. In summary, we hypothesize that a 5% lidocaine patch is an effective option for acute postoperative pain management following unilateral inguinal hernia repair, and it can be safely used in an outpatient clinical setting.

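### Every result with p < 0.05 is called significant, while a hoped-for post-discharge efficacy conclusion rests on unranked secondary outcomes alone

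*Protocol article*

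**What the plan says.** The Outcomes section names a single primary time point: "The primary outcome is pain intensity measured using the VAS at the time of discharge from the day surgery unit". This is about 2 to 3 h after surgery. The Hypothesis section concerns that time point alone.

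The later measures are secondary: "The secondary outcomes are pain intensity at 24 h and 1 week after surgery". At the 1-week visit the trial also records complication rates and "the total amount of oral combination analgesics used after discharge".

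The Data analysis section then applies one threshold to everything: "All results with a p-value of less than 0.05 will be considered as significant". The article gives no testing order among the secondary outcomes, no condition on the primary result and no statement that the post-discharge outcomes are only supportive.

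Two places look beyond the discharge hypothesis. The Abstract, under Discussion, says that the trial may provide evidence on acute pain "but also demonstrate the efficacy and safety of the patch for post-discharge pain management". The main Discussion section expresses the belief that "we will be able to provide evidence on its efficacy and safety for post-discharge pain management".

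**The concern.** The discharge VAS is taken before the patient goes home, so it cannot show what the patch does afterwards. A conclusion on post-discharge efficacy must come from the 24 h VAS, the 1-week VAS or the oral analgesic total. The stated rule would call a nominal p < 0.05 on any of these significant, whatever the primary shows and however many of the others show nothing.

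At stake is what the trial may conclude. With 14 to 16 patients per group, an isolated p < 0.05 on one of several secondary outcomes is a weak basis for an efficacy statement. The Outcomes section itself places the first-day assessment at a time by which, it says, the patch no longer relieves pain, so a lone difference there calls for particular caution.

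**Working it through.** **Group size and sidedness (Sample size calculation).** The inputs are 4.8 ± 1.4 against 3.1 ± 1.6, a difference of 1.7, and 80% power.
- Pooled SD = √((1.4² + 1.6²)/2) = √2.26 = 1.503. Standardised difference = 1.7/1.503 = 1.131.
- A two-sided 5% t-test needs 13.3, so 14 per group, which is the stated figure. A one-sided 5% t-test needs 10.4, so 11.
- Dropout: 14/0.9 = 15.6, so 16 per group, as stated.

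The Data analysis section does not give the sidedness of its 0.05. I take two-sided tests with 14 per group.

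**Number of post-discharge efficacy tests (Outcomes).**
- One VAS score per later visit: 24 h VAS + 1-week VAS + oral analgesic total = 3.
- VAS at rest, coughing and moving at both later visits: 2 × 3 + 1 = 7.

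**Chance of at least one false p < 0.05 when the patch has no post-discharge effect.** For k independent tests this is 1 − 0.95^k. For a false result favouring lidocaine it is 1 − 0.975^k, because half of each two-sided 5% lies on that side.
- k = 3: 1 − 0.95³ = 14.3%; favouring lidocaine, 1 − 0.975³ = 7.3%.
- k = 7: 1 − 0.95⁷ = 30.2%; favouring lidocaine, 1 − 0.975⁷ = 16.2%.

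The outcomes come from the same patients and will be correlated, which lowers these figures. The document gives no correlations, so those below are assumptions. The dependent cases come from simulated null trials with equally correlated normal outcomes, 14 per group and pooled t-tests.

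| Assumed correlation | 3 tests, any p < 0.05 | 7 tests, any p < 0.05 |
|---|---|---|
| 0 (formula) | 14.3% | 30.2% |
| 0.3 | 13.5% | 27.5% |
| 0.5 | 12.4% | 23.6% |
| 0.8 | 9.9% | 15.1% |

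For 3 tests, a false result favouring lidocaine has a chance of about 7% at correlation 0, 6.3% at 0.5 and 5.0% at 0.8.

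**Ratios for 3 tests.** Any false positive: 9.9/5 = 2.0 to 14.3/5 = 2.9. Favouring lidocaine: 5.0/2.5 = 2.0 to 7.3/2.5 = 2.9.

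**The case against.** The strongest reply is that the quoted sentence is a routine per-test threshold in a condensed article. Testing hierarchies for secondary outcomes are usually left to the analysis plan, and a single named primary with unadjusted secondaries is common in small trials. This would dispose of the point if the article were merely silent. It is not silent: it applies one rule to all results and also names a post-discharge conclusion that the primary cannot support.

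The other objections limit how far the point goes, and they stand:
- **A reader might infer that the protocol promises to demonstrate post-discharge efficacy.** It does not. In the Abstract the verb is governed by *may*, and the main Discussion speaks of a belief that evidence will be provided.
- **A reader might infer that any one significant secondary would establish the claim, or could replace a failed primary.** No section says so. The any-one-of-three reading is an assumption on which all the percentages rest.
- **A reader might take 7 tests as the planned number.** The sentence "We will evaluate each patient’s VAS scores in three situations: at rest, when coughing, and when moving" follows directly on the primary outcome, and the later visits are described with a single VAS score. Seven tests are possible but not stated.
- **A reader might add the remaining secondaries to the count.** Intraoperative opioid use, "time to recovery, and pain intensity at 30 min after surgery as a part of the secondary outcomes", are not post-discharge measures and have no bearing on this claim.
- **The directional error of 5% to 7% looks close to 5%.** That is fair in absolute terms. The like-for-like comparison for one two-sided test at 0.05 is 2.5%, so the two- to threefold increase remains.

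**Conclusion.** The point holds in a limited form. The rule in the Data analysis section lets a nominal p < 0.05 on any post-discharge secondary be called significant, and those outcomes alone can carry the post-discharge conclusion that the authors hope for.

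On the 3-test reading that the text best supports, the error for that conclusion is about two to three times nominal: roughly 10% to 14% for any false positive, and 5% to 7% for one favouring lidocaine. It reaches 15% to 30% only if all three VAS situations are tested at both later visits. These figures assume two-sided tests, correlations between 0.8 and 0, and that one significant outcome would be taken as enough.

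The document does not support the stronger inference that the trial's main test is compromised. The primary is one named time point, and testing secondaries beside it does not change its type I error.

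**What to change.** Replace the last sentence of the Data analysis section with wording such as: *Only the primary outcome is tested confirmatorily, at the stated alpha. Secondary outcomes are supportive and are reported as between-group differences with 95% confidence intervals; any p-values for them are nominal.* In the Abstract, change *demonstrate* to *explore*. The softer sentence in the main Discussion can then be read consistently with this.

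If a confirmatory post-discharge claim is wanted, name one post-discharge outcome and test it at the same alpha only if the primary succeeds, with the other secondaries supportive. This fixed order keeps the error over the two tests at the stated alpha without changing the sample size.

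The cost is a few words, with no extra patients, visits or data. The small downside is that an isolated secondary p < 0.05 can no longer be presented as demonstrated efficacy.

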### Data monitoring

The principal investigator will report any unexpected problems or non-compliance with the protocol to the participant in question, the Institutional Review Board of Seoul National University Bundang Hospital, the Ministry of Food and Drug Safety, and the reviewing committee, if necessary. If an adverse drug reaction is the cause of death or is life-threatening, the initial report should be submitted within 7 days. If an adverse drug reaction is not fatal, the initial report should be submitted within 15 days. Minor non-compliance cases should be reported every year on a case-by-case basis.

### Ethics and dissemination

Collected information for research will be stored in a locked file in a laboratory, and access to the research file will be restricted to authorized researchers. Unnecessary personal data will be removed, and information such as patient’s name, resident registration number, and medical chart number should not be recorded. The identifying codes linked to personal information will be managed separately. The records of the participants will be kept confidential and will not be moved to other places, and may be sent, if necessary, to an authorized person for supervision of this study.

We will disseminate the methods and results of our study to the public through social media, presentations at domestic and international congresses on corresponding areas of interest, and by submitting a paper(s) describing our findings to appropriate scientific journals.

## Discussion

Targeted topical analgesics such as 5% lidocaine patches have been known to improve acute and chronic pain [7, 11]. Previous studies have investigated the effects of lidocaine patches on postoperative pain management following various surgeries. Most of these studies included patients with small trocar wounds after laparoscopic surgeries, such as laparoscopic appendectomy, ventral hernia repair, and gynecologic surgery. A prospective study of 40 patients who underwent laparoscopic appendectomy in whom a lidocaine patch was applied at the umbilical trocar site showed that a 5% lidocaine patch might be effective for managing port-site pain [12]. Another study of 30 patients who underwent laparoscopic ventral hernia repair also found that lidocaine patches are effective for postoperative pain management [9]. A study of 40 patients who underwent laparoscopic gynecologic surgery found that patients who received a lidocaine patch had lower VAS scores and additional analgesic requirement than those who did not receive a lidocaine patch [10].

There are a few studies in which a lidocaine patch was used postoperatively for incisions that were longer than a trocar incision. In a randomized controlled trial of 70 patients who underwent radical retropubic prostatectomy with a lower midline incision, a lidocaine patch was applied for 24 h after the surgery, resulting in reduced pain scores and opioid consumption [13]. A similar trial conducted on 28 patients who underwent open gynecological surgery with a midline incision found that postoperative pain reduced with lidocaine patch use [14].

Through these studies, which included randomized clinical trials and meta-analyses, the safety and efficacy of using a 5% lidocaine patch for acute postoperative pain management has been established. However, most of these studies were on patients who received hospital care and patient-controlled analgesia following surgery, in which the patients’ acute pain was rapidly treated by medical staff. However, the lidocaine patch has advantages comparing with other operative pain managements, such as abdominal muscle fascia and peritoneal nerve block and patient-controlled analgesia. It is non-invasive and simple to apply since the lidocaine patch may produce an analgesic effect without a complete sensory blockage by penetrating skin depth of only 8 to 10 mm [15]. The lidocaine patch may also have a great safety profile for application in an outpatient clinical setting for acute postoperative pain.

We have designed this clinical trial to investigate the efficacy of a 5% lidocaine patch for postoperative pain management without additional medical attention. Therefore, we will enroll patients undergoing open unilateral inguinal hernia repair at a day surgery unit. We believe that in addition to demonstrating the efficacy of a 5% lidocaine patch on acute postoperative pain after unilateral inguinal hernia repair, we will be able to provide evidence on its efficacy and safety for post-discharge pain management. In summary, we hypothesize that a 5% lidocaine patch is an effective option for acute postoperative pain management following unilateral inguinal hernia repair, and it can be safely used in an outpatient clinical setting.

## Trial status

This protocol version 1.0 was first posted on February 15, 2021, in Clinicaltrials.gov, without any amendments after then. Patient recruitment commenced in March 2021, and the predicted date of completion of this study is October 2021.

## Data Availability

Not applicable

## Abbreviations

VAS: Visual analog scale
